31 participate to assess their satisfaction level towards the procedure. The primary outcome is  
32 child-reported pain. Secondary outcomes include child-reported anxiety, heart rate, salivary  
33 cortisol, length of procedure, and satisfaction of health care providers with respect to the  
34 venipuncture procedure. The cost-effectiveness of IVR intervention will be compared with  
35 that of standard care. Outcome evaluation will be conducted at four time points: 10 minutes  
36 before, during, and immediately after and 30 minutes after the procedure. Intention to treat  
37 and generalized estimating equation model will be used to analyze the data.

38 This study is the first of its kind to adopt IVR intervention with age-appropriate  
39 procedural information for pediatric patients undergoing venipuncture. Findings of the  
40 proposed study may (1) provide a novel, facile, and cost-effective intervention that can be  
41 used virtually at any time and place to manage pain and anxiety; and (2) shed light on the  
42 global trends of research and clinical development of IVR as an intervention for other painful  
43 and stressful medical procedures.

44

45

46

47

48

49

50

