## **Theoretical Frameworks**

The Gate Control Theory and Lazarus and Folkman's theory provide the theoretical underpinning of this study [26-27]. The gate control theory suggests that peripheral nerves

become excited when cells are damaged. Impulses from nerves pass along to spinal cord systems and other neuroanatomical structures before reaching the cerebral cortex where pain is perceived. The gate control system in the spinal cord opens and closes to modulate pain perception. If non-nociceptive input (IVR) exceeds the nociceptive (pain) input, then the gate can partially or entirely close, blocking the transmission of the pain signal to the brain. The theory also proposes that pain signals that descend from the brain through the gate can be amplified by emotional experiences, such as anxiety and stress. Lazarus and Folkman's theory [27] states that an individual's evaluations of anxiety and stress-provoking experiences are influenced by their perceptions of control over a potential threat. Providing information may help improve pediatric patients' sense of control over a procedure [18-19, 28].

In the context of these two theories, IVR functions by providing multisensory input to divert the children's conscious attention from venipuncture-associated pain, thus helping close gate control and decreasing pain perception [29]. The analgesic effects of IVR have been supported by the results of functional magnetic resonance imaging assessment [30]. Providing procedural information through IVR modules further help increases the children's sense of control over the procedure, thereby reducing their stress and anxiety, as well as pain signals transmitted through the gate control system. Therefore, IVR intervention will likely reduce pain, anxiety and stress; these changes are evidenced by physiological changes in the heart rates and salivary cortisol levels of the patients. Thus, patients may show increased procedural compliance, consequently decreasing the length and cost of the procedure while possibly improving the satisfaction of the health-care providers with the procedure [5, 10].

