#### **Randomization**

Eligible participants will be randomly assigned in a 1:1 ratio to the intervention group who will receive the IVR intervention or a control group that will receive standard care only using stratified permuted block randomization with a block size of 10 to maintain a good balance of participants between the two groups throughout the subject recruitment period. Randomization will be stratified by age group (4–7; 8–12 years old) in equal numbers.

According to Piaget’s theory, children from 4 years to 7 years of age belong to the same pre-operational stage, whereas those in the age range 8–12 years belong to the concrete operational stage [31]. Children in different stages differently perceive information and pain stimuli sensitivity [32].

A sequence of grouping identifiers (I=intervention group or C=control group) will be prepared in advance by an independent statistician, using computer-generated random codes for each of the two strata of age group. The group identifiers for each age group will then be put in serially numbered sealed opaque envelopes according to the underlying random sequence list by the statistician. The group allocation of the patients will be assigned according their ages, sequence of enrolment in the study, and the group identifier contained in the corresponding numbered envelopes. Group allocation will be concealed from the research assistant (RA), ward staff, child, and parents/ legal guardians until consent and baseline assessment data has been obtained. Given the nature of the intervention, blinding of participants, RA, and health care provider will be difficult. Nevertheless, the lack of blinding will not necessarily contribute to a source of bias because children are unlikely to change their behavior even when they know they are participating in a certain intervention [33].

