#### **Implementation Protocol**

The venipuncture procedure will be conducted in the treatment room while parents/ legal guardians wait outside. Patients assigned to the intervention group will receive IVR intervention prior to the start of venipuncture until the end of the procedure [11, 23]. The RA will provide simple and standard instruction on how to use the equipment. The headset will then be placed on patient’s head and adjusted to ensure a comfortable and secure fit. Patients will be allowed to view the IVR module according to their age group (4–7 years, 8–12 years). During the intervention, the control of the IVR module will only be achieved by the head movement of the patients. The patients will also be told that the intervention will be discontinued if they experience motion sickness, eye discomfort, or headaches.

After receiving IVR intervention, the RA will invite the doctor/phlebotomist to start the venipuncture. The beginning of the procedure is indicated by doctor/ phlebotomist disinfecting the venipuncture site. The RA will note the time of first attempt at venipuncture. The end of the procedure is indicated by application of band aid to the venipuncture site. The RA will remove the IVR equipment from the child after the procedure. The protocol follows for the first venipuncture attempt only. If the first attempt is unsuccessful, additional attempts occurring after the protocol will be completed, but participants will be counted as unsuccessful case of the study.

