### **Outcome Measures**

#### **Primary outcome**

***Faces pain scale-revised:*** The FPS-R scale is a 0 to 10 scale comprising six horizontally arranged cartoon faces with expressions of “0 = no pain” to “10 = very painful” [39]. Participants will be asked to point to the face that indicates how much pain she/he feels. The protocol for use of FPS-R is standardized and is a reliable and valid scale for evaluating pain in children [9, 11].

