#### **Data Collection Procedures**

Children requiring venipuncture will be identified by the nurse in the pediatric unit. If the children meet the inclusion criteria for recruitment, the nurse will refer the children and their accompanying parents/ legal guardians to the RA in the treatment room, who will give them an information sheet, explain the study and show the IVR equipment. If they agree to participate, written informed consent from the accompany parents/ legal guardians and assent from the children will be obtained. The RA will then acquire socio-demographics information from the parents/ legal guardians and clinical characteristics of the children from medical record before randomization. According to the subject allocation scheme, children in the control group will receive standard care, whereas those in the intervention group will additionally receive IVR intervention.

Participants will be assessed:10 minutes prior to the procedure (T0), during the procedure when the needle insert to the skin (T1), immediately after the procedure indicate by application of band aid to the venipuncture site (T2), and 30 minutes after the procedure (T3). At T0, a set of baseline data - saliva sample for a measure of cortisol, FPS-R, VAS for anxiety, CSAS-C, and heart rate - will be collected from the patients by the RA. At T1, heart rate will be obtained. At T2, FPS-R, VAS for anxiety, CSAS-C and heart rate will be obtained from children. At the same time, the RA will record the length of procedure and invite the health care providers involved to fill in the staff satisfaction scale. At T3, saliva sample for a measure of cortisol, FPS-R, VAS for anxiety, CSAS-C, and heart rate will be obtained from patients again. Please refer to table 1 and figure 1.

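### The reason given for discounting bias from lack of blinding does not fit a self-reported primary outcome, and showing every child the headset before randomization adds avoidable contrast

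*Protocol*

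**What the plan says.** **Blinding.** Protocol, Randomization, states: "Given the nature of the intervention, blinding of participants, RA, and health care provider will be difficult". It continues that "the lack of blinding will not necessarily contribute to a source of bias because children are unlikely to change their behavior", citing a review of therapeutic play. Allocation is concealed from the RA, ward staff, child and parents "until consent and baseline assessment data has been obtained", so the ratings after baseline are open.

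**Primary outcome.** Child-reported pain (Abstract). Under Primary outcome: "Participants will be asked to point to the face that indicates how much pain she/he feels". The same paragraph says that use of the scale is standardized.

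**The RA's roles.** Under Implementation Protocol the RA gives "simple and standard instruction on how to use the equipment" and takes the headset off afterwards. Fidelity of the Intervention describes one RA, trained both to deliver the intervention and to collect data. Data Collection Procedures names the RA as collector at T0. For the ratings at T2 and T3 it uses the passive voice and names nobody, although at T2 it has the RA recording procedure length at the same moment.

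**What children see before allocation.** Data Collection Procedures has the RA "explain the study and show the IVR equipment" to the child and parents before consent and randomization. Control children then receive standard care without IVR.

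**Theory.** Theoretical Frameworks holds that pain signals can be "amplified by emotional experiences, such as anxiety and stress".

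**The concern.** An open design cannot be avoided here, and the protocol discloses it. The weakness is in the reasoning and in one avoidable step.

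First, the stated reason concerns whether children change their behaviour. A face chosen on request can move for other reasons: the child expects the headset to help, is disappointed not to get it, or responds to the manner of an adult who knows the arm. The sentence addresses none of these.

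Second, the person asking is apparently the person who fitted and removed the headset.

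Third, showing the device to everyone and then giving it to half makes it vivid to control children what they did not receive.

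These influences would plausibly all favour IVR. The trial seeks a difference of only 0.8 points on a 0–10 scale, so a modest shift would matter. The cost-effectiveness ratio is built on the same FPS-R change and would carry any such shift with it.

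**Working it through.** **Inputs from the protocol.** Difference 0.8, SD 1.84, 80% power, 5% significance, 85 per group, inflated to 200 and then 250 (Sample size – Patients). Tests are two-sided (Data analysis). FPS-R: six faces scored 0 to 10 (Primary outcome), so equal steps are 10/5 = 2 points.

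**The plan's own figure.** A two-sided comparison of two means with these inputs needs 84 per group by the normal formula and 84.01 by the t-test, which rounds up to 85. Then 170/0.85 = 200 and 200/0.80 = 250. The sample size reproduces; there is no numerical error in it.

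**Sensitivity to a reporting shift (assumption only).** Suppose IVR has no true effect and reporting alone moves a fraction of children by one face between arms:

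- 1 child in 20: 2/20 = 0.1 points, or 0.1/0.8 = 12.5% of the target
- 1 child in 10: 2/10 = 0.2 points, or 25%
- 1 child in 5: 2/5 = 0.4 points, or 50%

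Standard error of the difference at 85 per arm: SE = 1.84 × √(2/85) = 0.282. The smallest significant difference is 1.96 × 0.282 = 0.55 points.

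Rejection probability under a pure shift b: Φ(b/SE − 1.96) + Φ(−b/SE − 1.96).

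| Shift b | b/SE | Significant in favour of IVR (nominal 2.5%) | Two-sided total (nominal 5%) |
|---|---|---|---|
| 0.1 | 0.354 | 5.4% | 6.45% |
| 0.2 | 0.709 | 10.5% | 10.9% |
| 0.3 | 1.063 | 18.5% | 18.6% |
| 0.4 | 1.417 | 29.4% | 29.4% |

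More children do not help, because the shift stays while the SE shrinks. If all 125 per arm contributed, SE = 1.84 × √(2/125) = 0.233, and a 0.4-point shift would give 40.5%.

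**Who takes the ratings.**

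- T0: the RA, stated, and before allocation is revealed.
- T2: not named. The RA is present and recording, and parents are outside the room.
- T3: not named. No other assessor appears anywhere in the protocol, and the one RA described is trained to collect data.

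That the RA takes all three ratings is therefore a strong inference and not a statement of the protocol.

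**The case against.** **The protocol is candid and hedged.** It says blinding will be difficult and that bias will not *necessarily* follow. A reader might infer that it denies bias altogether; the wording does not support that. The source cited for the argument is not at hand, and pointing to a face is itself a kind of behaviour. This softens the criticism, but the sentence still offers no answer on expectation or interviewer influence.

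**Safeguards exist.** Baseline ratings are protected by concealment. FPS-R use is described as standardized. Heart rate, salivary cortisol and stopwatch time are less open to reporting bias, and the theory section already treats heart rate and cortisol as corroboration. All this stands. But standardized use of a scale is not a safeguard against an asker who knows the arm, and the physiological measures are secondary.

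**Disappointment may cause real pain.** If emotion amplifies pain, a disappointed control child may feel more pain, and that is not reporting bias. Lowering anxiety is also part of how IVR is meant to work. This stands. What remains is that a reaction to being shown and not given the device is not part of ordinary standard care, so it would widen the contrast between arms for a reason outside the intervention. Nothing in the documents shows that such reactions occur.

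**The demonstration serves consent.** A reader might infer that it is redundant because IVR children are instructed later. The two steps have different purposes: one informs parents and child before assent, the other teaches use of the device. Moving it has a cost, and control children would still know that IVR exists.

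**Conclusion.** The point holds in a limited form. The justification under Randomization does not fit a self-reported primary outcome that is apparently collected by the unblinded RA who delivers IVR, and Data Collection Procedures adds contrast between arms that could be reduced at little cost.

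The size of any bias cannot be derived from the protocol. The rise from 5% to about 6% to 29% rests wholly on assumed shifts of 0.1 to 0.4 points, no true effect, SD 1.84 and 85 per arm. It shows how sensitive a 0.8-point target is; it is not evidence that bias of this size will occur. Nor do the documents support the stronger reading that a positive FPS-R result would be uninterpretable. The trial remains worth running as designed. The safeguards are an inexpensive improvement, but they need to be in place before enrolment because they cannot be added at analysis.

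**What to change.** 1. **Data Collection Procedures.** Explain IVR before consent with the information sheet or a picture. Show the device only to children allocated to IVR, after the envelope is opened. Cost: wording of the protocol and consent script, and assent given without seeing or handling the device. This reduces control children's awareness of IVR but does not remove it.

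2. **Primary outcome, Secondary outcomes and Data Collection Procedures.** Collect FPS-R, the anxiety VAS and CSAS-C at T0, T2 and T3 with one identical pre-recorded prompt in both arms, and state who takes the ratings at T2 and T3. Cost: a short recording for each instrument and no extra staff. The RA would still be present, so influence through manner is reduced and not eliminated.

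3. **Randomization.** Replace the sentence on children's behaviour with a statement that self-reported outcomes are open to expectation and interviewer bias, and that heart rate and cortisol are supportive evidence only. Cost: one sentence. By itself this changes the interpretation and not the bias, so it should accompany the first two changes.

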#### **Control Group: Standard Care**

Participants in the control group will receive standard care without IVR intervention. Standard care includes explaining why and what is being done and saying comforting and supportive words during procedures.

#### **Intervention: IVR**

In addition to standard care, children in the intervention group will receive IVR intervention through a commercially available VR headset, which can be fitted into majority of commonly available smartphones. Although other latest headsets, such as Oculus Rift or HTC Vive, can provide high quality of immersion experience, they likewise increase the risk

of contact infection and require a high spectrum personal computer to operate. Therefore, these devices will not be used in this study.

With regard to the IVR modules, previous work conducted by lead PI's research team selected five modules for patients. Examples of these modules include interactive games, cartoon animation, and animated scenery. Among these modules, cartoon animation and interactive games were considered interesting by patients and can capture their attention for an extended period of time. For instances, cartoon animation was preferred by young patients, whereas the interactive game was preferred by adolescents; these results concurred with a previous study [25]. An IVR module that presents procedural information through a customized and child-friendly design more effectively mitigates pain and distress than that with off-the-shelf content [18, 30, 34]. However, these freely downloaded IVR modules that were developed in Western countries with English as the medium may not be completely appropriate for pediatric patients in Hong Kong. In the proposed study, IVR modules have been designed on the basis of suggestions to use age-appropriate modules for patients [16-17] and the experiences of the lead PI, who has successfully developed six cartoon animations in previous studies [35]. The lead PI has produced two developmentally appropriate IVR modules: One for 4–7 year-old children and one for 8–12 year-old children. The two modules share the following common characteristics with those used in previous studies: (1) a wide range of visual and auditory stimuli [11, 23-24]; (2) requiring minimum movement of head and hand to allow the procedures to proceed unhindered [36]; and (3) provision of procedural information. Both modules have been validated by an expert panel and used in pediatric cancer patients during venipuncture.

#### Module for children aged 4 to 7 years

For children 4–7 years of age, their comprehension of words and sentences is not well-established. However, their curiosity and imaginative thinking are developed [37]. On the

contrary, visual stimulation may be effective in distracting the children [28, 38]. Thus, this VR module presents fast-paced zooming of the screen with cartoon characters enacting various body movements [38]. Pastel tone colors which are less tiring to the eyes are used to provide visual stimulation. The animation “DD is in the hospital” uses simple words and sentences to provide procedural information to the pediatric patients as to why the cartoon character “DD” needs a venipuncture in a child-focused manner. The VR module aims to provide distraction as well as instill a sense of control by exposing patients to the procedure [7, 28, 30].

#### Module for children aged 8 to 12 years

The main goal of this module is to create an interactive environment for distracting children during venipuncture. The animation will prepare children for venipuncture by providing information, such as (1) why the procedure must be done; (2) what will happen; and (3) how the procedure will feel. The VR module will be followed by an interactive game to increase patients’ sense of control over the procedure. In this game, the patients will assist to find out equipment for performing venipuncture in the IVR environment [28, 38].

#### **Implementation Protocol**

The venipuncture procedure will be conducted in the treatment room while parents/ legal guardians wait outside. Patients assigned to the intervention group will receive IVR intervention prior to the start of venipuncture until the end of the procedure [11, 23]. The RA will provide simple and standard instruction on how to use the equipment. The headset will then be placed on patient’s head and adjusted to ensure a comfortable and secure fit. Patients will be allowed to view the IVR module according to their age group (4–7 years, 8–12 years). During the intervention, the control of the IVR module will only be achieved by the head movement of the patients. The patients will also be told that the intervention will be discontinued if they experience motion sickness, eye discomfort, or headaches.

After receiving IVR intervention, the RA will invite the doctor/phlebotomist to start the venipuncture. The beginning of the procedure is indicated by doctor/ phlebotomist disinfecting the venipuncture site. The RA will note the time of first attempt at venipuncture. The end of the procedure is indicated by application of band aid to the venipuncture site. The RA will remove the IVR equipment from the child after the procedure. The protocol follows for the first venipuncture attempt only. If the first attempt is unsuccessful, additional attempts occurring after the protocol will be completed, but participants will be counted as unsuccessful case of the study.

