#### **Sample size – Patients**

In 2016, about 250 hospitalized patients aged between 4 years to 12 years were admitted to the unit and required venipuncture. Sample size estimation was based on the effect estimated from a previous IVR study using the FPS-R Scale as a primary outcome measure [11]. By using the power analysis software, GPower 3.1, it was estimated that a sample size of 85 participants per group would enable a 2-arm RCT to detect a between-group difference of 0.8 in FPS-R scale with a pooled standard deviation of 1.84 with 80% power at 5% level of significance. Taking into account of up to 15% attrition rate [24], 200 children will be recruited. Furthermore, to account for those who fail in the first attempt of venipuncture, the total sample size is adjusted to 250 children to be recruited with the estimation of 20% of unsuccessful cases in the first attempt. As such, the total recruited number of children will be 250 for the experimental and control groups, with 125 children in each group.

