**Length of procedure:** A standard stop watch will be used to measure the length of the procedure from the beginning (time when the doctor/phlebotomist starts to disinfect the site) to the end of procedure (time when applies the band aid on the venipuncture site).

**Staff satisfaction scale:** The staff satisfaction scale will be adopted to measure the satisfaction levels of the health care providers toward the procedure [45]. It consists of 8-item and each rated by a 5-point scale ranging from 1 = strongly disagree to 5 = strongly agree. Higher score presents a higher level of the satisfaction. This scale has been translated by the PI using back-translation method recommended by Brislin (1970) and used in a previous study with the Cronbach's alpha of 0.90 [41].

**Cost-effectiveness:** Cost analysis will be examined based on incremental cost-effectiveness ratio expressed as incremental cost per every one unit decrease in the primary outcome of the FPS-R scale immediately post-intervention with respect to the baseline. All the cost data involved will be expressed in Hong Kong dollars and valued on the starting date of the study on the basis of non-subsidized cost. All costs incurred will be estimated per each participant using the method of Thompson & Barber [46]. Specifically, the cost of human resources (e.g. doctors, nurses, phlebotomist, and health care assistants) is measured by the salary of the middle rank of the professionals and calculated based on the minutes used to perform the procedures. Costs of consumables to perform the venipuncture (e.g. alcohol pad, glove, butterfly needles, and band aid) will be based on the retail price paid by the finance office of the hospital. In addition, the cost for development of IVR modules and VR goggles will be included in the intervention group.

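### No timing rule covers a failed first attempt: repeat-attempt time and cost go uncaptured, or about 50 children are set aside against intention to treat

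*Protocol*

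**What the plan says.** **Scope.** Protocol, Implementation Protocol: "The protocol follows for the first venipuncture attempt only". Later attempts are placed after the protocol, and after a failed first attempt "participants will be counted as unsuccessful case of the study".

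**Clock.** The same section starts and ends the procedure as follows: "The beginning of the procedure is indicated by doctor/ phlebotomist disinfecting the venipuncture site"; "The end of the procedure is indicated by application of band aid to the venipuncture site". Under Secondary outcomes, length of procedure is stopwatch time over the same interval, ending at the "time when applies the band aid on the venipuncture site".

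**Assessment times.** Data Collection Procedures takes T2 at the band aid and T3 30 minutes after the procedure. The research assistant records the length at T2.

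**Expected failures.** Sample size – Patients goes from 200 to 250 children with "the estimation of 20% of unsuccessful cases in the first attempt".

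**Analysis.** Data analysis adopts intention to treat for the outcome comparisons.

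**Use of the measure.** Hypothesis 1 claims a shorter procedure. The cost analysis values staff by the minutes spent on the procedure and adds consumables.

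**The concern.** The definition works for a child whose blood is drawn at the first attempt. For a child whose first attempt fails, the text does not say whether the clock stops at a band aid on that first site, runs to the final band aid, or yields no analysable time.

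Two outcomes depend on the answer. Length of procedure is named in Hypothesis 1, and staff cost is computed from procedure minutes. The rationale under Theoretical Frameworks links the two: "patients may show increased procedural compliance, consequently decreasing the length and cost of the procedure". If repeat attempts fall outside the measurement, neither outcome describes the time or cost of obtaining the sample. If the two arms differ in first-attempt success, in either direction, part of that difference is missing from the comparison.

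This cannot be left to a later analysis plan. Stopwatch time and attempt counts that were not recorded cannot be recovered. The research assistant who stops the watch also knows the allocation, so an improvised rule could be applied differently in the two arms.

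**Working it through.** **1. The plan's own figure.** Inputs from Sample size – Patients: difference 0.8, SD 1.84, 80% power, 5% level (two-sided, from Data analysis).
- The exact t-test calculation gives 85 per arm (power 80.5%), so 2 × 85 = 170.
- Attrition of 15%: 170 / 0.85 = 200.
- First-attempt failure of 20%: 200 / 0.80 = 250.

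All stated figures reproduce. The last step means that 0.20 × 250 = 50 children are planned as not contributing.

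**2. The possible readings for those 50 children.**
- *Clock stops at attempt one.* This fits the first-attempt scope. Repeat-attempt minutes and consumables are left out.
- *Child set aside.* This fits the unsuccessful-case label and the 200 / 0.80 step. It conflicts with intention to treat and selects on an event after randomisation.
- *Clock runs to the final band aid.* This captures everything but goes beyond the first-attempt scope. T2, and with it the FPS-R score, then follows more than one needle.

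No section chooses among them.

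**3. Effect on the comparison.** The documents give no durations, so this step is illustrative. Let S be the time for a first-attempt success, F the time to the end of a failed first attempt, T the time to the final band aid when the first attempt fails, and p the failure rate. Assume no true effect on S.
- Mean, clock stopped at attempt one: (1 − p)S + pF
- Mean, clock run to the final band aid: (1 − p)S + pT
- IVR minus control: (pC − pI)(S − F) and (pC − pI)(S − T) respectively
- Difference hidden by stopping at attempt one: (pC − pI)(T − F)

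If a repeat attempt adds T − F = 5 to 10 minutes (assumption):
- Mean time omitted per randomised child at p = 0.20: 0.20 × 5 = 1.0 to 0.20 × 10 = 2.0 minutes.
- Difference hidden at a 10-point gap in failure (assumption): 0.10 × 5 = 0.5 to 0.10 × 10 = 1.0 minute.
- Difference hidden at equal failure: 0.

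Assumed values S = 5, F = 3, 5 or 7, and T = 10 or 15 minutes, IVR minus control:

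| Failure, control / IVR | Stop at attempt one | Failures excluded | To final band aid |
|---|---|---|---|
| 20% / 20% | 0 | 0 | 0 |
| 25% / 15% | +0.2, 0.0, −0.2 | 0 | −0.5 (T = 10), −1.0 (T = 15) |
| 15% / 25% | −0.2, 0.0, +0.2 | 0 | +0.5 (T = 10), +1.0 (T = 15) |

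The choice of rule matters to the comparison only when failure differs by arm. Even with equal failure it shifts the level: at 20% in both arms the mean is 4.6 to 5.4 minutes stopped at attempt one, against 6.0 to 7.0 minutes timed to the end.

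**The case against.** The strongest reply is that first-attempt duration is a legitimate outcome. It covers the period in which the randomised intervention is delivered, and less struggling within a single attempt fits the stated compliance mechanism as well as fewer repeats would. That stands as a reason to keep first-attempt duration. It does not settle what is recorded for a failed attempt, and it does not serve a cost analysis meant to reflect the resources used.

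Several stronger readings are tempting, but the documents do not support them:
- *A failed attempt is logged as a short, finished procedure.* The text labels the child an unsuccessful case, and the 200 / 0.80 step treats such children as lost. No duration is given, and a failed attempt may take longer than a clean draw.
- *The length conclusion would point the wrong way.* In the illustration the sign reverses only when failed attempts are assumed shorter than successful ones and failure differs by arm.
- *The benefit acts mainly through fewer repeat attempts, or the headset causes failures.* Neither is stated. The intervention section says the modules need little head or hand movement so that the procedure is not impeded.
- *The protocol contradicts itself on when IVR ends.* Read together, the headset comes off at the end of a procedure that comprises the first attempt, with later attempts outside it. A conflict appears only if repeat attempts are read into the word procedure.

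It is also fair to say that this touches a secondary outcome and the cost analysis, and that the failure rate may turn out equal in the two arms.

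**Conclusion.** The point holds as a gap in outcome definition combined with a conflict over who is analysed. For an expected 20% of children, about 50 of 250, the protocol as written either leaves repeat-attempt time and consumables uncaptured or sets the child aside, against its own intention-to-treat principle. In both cases length of procedure and staff-minute cost do not measure the time and cost of obtaining the sample.

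The comparison is distorted only if first-attempt failure differs by arm, and the size cannot be derived from the documents. The 0.5 to 1.0 minute figure rests on two assumptions: 5 to 10 added minutes and a 10-point gap in failure. No direction of bias is established. The sample size is unaffected, because length of procedure was not its basis. The matter should be settled before recruitment because the missing data could not be reconstructed.

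**What to change.** - **Implementation Protocol and Length of procedure:** time every randomised child from first disinfection to the final band aid. Also record the number of attempts and the end time of attempt one.
- **Data analysis and Cost-effectiveness:** analyse total length and total cost, including all consumables, in all randomised children. Report first-attempt duration and first-attempt success by arm as supporting results. State that the unsuccessful-case label does not remove a child from these comparisons.
- **Data Collection Procedures:** state one T2/T3 anchor for children with more than one attempt, the same in both arms. There is a trade-off: questionnaires taken between attempts would add to the running clock, and an anchor at attempt one can put a later needle inside the 30 minutes before T3. The choice should be explicit.

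The cost is a few sentences, two extra data fields, and a stopwatch left running with a split time noted. The statistical downside is a more skewed and more variable length outcome. Recording the end of attempt one keeps the narrower measure available.
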